## Abstract

**Background:**

Cardiovascular risk management is largely provided in primary healthcare, but not all patients with established cardiovascular diseases receive preventive treatment as recommended. Accreditation of healthcare organizations has been introduced across the world with a range of aims, including the improvement of clinical processes and outcomes. The Dutch College of General Practitioners has launched a program for accreditation of primary care practices, which focuses on chronic illness care. This study aims to determine the effectiveness and efficiency of a practice accreditation program, focusing on patients with established cardiovascular diseases.

**Methods/design:**

We have planned a two-arm cluster randomized trial with a block design. Seventy primary care practices will be recruited from those who volunteer to participate in the practice accreditation program. Primary care practices will be the unit of randomization. A computer list of random numbers will be generated by an independent statistician. The intervention group (n = 35 practices) will be instructed to focus improvement on cardiovascular risk management. The control group will be instructed to focus improvement on other domains in the first year of the program. Baseline and follow-up measurements at 12 months after receiving the accreditation certificate are based on a standardized version of the audit in the practice accreditation program. Primary outcomes include controlled blood pressure, serum cholesterol, and prescription of recommended preventive medication. Secondary outcomes are 15 process indicators and two outcome indicators of cardiovascular risk management, self-reported achievement of improvement goals and perceived unintended consequences. The intention to treat analysis is statistically powered to detect a difference of 10% on primary outcomes. The economic evaluation aims to determine the efficiency of the program and investigates the relationship between costs, performance indicators, and accreditation.

**Discussion:**

It is important to gain more information about the effectiveness and efficiency of the practice accreditation program to assess if participation is worthwhile regarding the quality of cardiovascular risk management. The results of this study will help to develop the practice accreditation program for primary care practices.

**Trial registration:**

This cluster randomized trial is registered at ClinicalTrials.gov nr NCT00791362

## Background

Cardiovascular diseases (CVD) remain an important cause of mortality and morbidity worldwide. In public health and in primary care, many efforts have been made to prevent CVD [1,2]. Although cardiovascular care has improved in recent years [3], a substantial number of individuals receive suboptimal cardiovascular risk management (CVRM) and do not attain the lifestyle, risk factor, and therapeutic targets that are recommended [4,5]. A range of interventions to improve healthcare delivery is available [6-8]. In recent years, programs have been developed for performance indicators, accreditation, pay-for-performance, and public reporting [9]. These approaches make use of market forces and pressure for accountability, but research evidence on effectiveness and efficiency is limited [9-11].

The slow improvement of cardiovascular primary care may be caused by the one-off and condition-specific character of many improvement activities (*e.g.*, a continuing education session or audit without follow-up). To enhance continuous improvement in primary care in the Netherlands, the Dutch College of General Practitioners (DCGP) initiated in 2005 a nationwide comprehensive practice accreditation program for primary care practices. This program consists of a systematic audit on the basis of validated performance indicators for diabetes mellitus, CVRM, asthma, chronic obstructive pulmonary disease (COPD), practice organization, patient experience, educational feedback to practices, the requirement to develop structured improvement plans, and a check on the implementation of these plans after one year. If the procedure is performed, primary care practices receive a certificate that provides accreditation for a time period of one year. While accreditation serves a range of purposes, improvement of professional performance and practice organization are prominent among these [12-14]. While the impact of audit and feedback is mixed and moderate [15], it is unknown what the added value of the accreditation procedure is. A study of practice accreditation in German primary care practices showed that it improved aspects of practice organization, but this study did not measure or assess impact on clinical processes or outcomes [16]. Given the resources invested in accreditation schemes and the high expectations, an evaluation of the impact on quality and outcomes of care is needed.

A substantial number of performance indicators used in the practice accreditation program is related to CVD. These indicators are derived from the completely revised guideline on CVRM that was published by the DCGP late 2005 [17]. The new set of guidelines on CVRM describes the clinical interventions to be implemented in patient care in this project. They contain important changes in recommendations, such as different cut-off levels (*e.g.*, LDL-cholesterol <2.5 mmol/l and systolic blood pressure <140 mmHg). The DCGP has developed a number of products and activities to implement these guidelines, including a national kick-off conference for general practitioners (GPs) in December 2005, and a supportive package (‘kwaliteitskoffer’) consisting of educational materials and software for assessment of cardiovascular risk. The practice accreditation program is an important approach to improve primary care, but controlled evaluations of its effect have not yet been done.

### Aims and objectives

The overall aims of the study are to determine the effectiveness and efficiency of the practice accreditation program in primary care, focused on its effect on CVRM.

Key objectives are:

1. To determine the effectiveness of the program on primary performance indicators for CVRM by comparing practices in the accreditation program that focus their improvement plans on CVRM to practices in the accreditation program that focus their improvement plans on other domains of chronic care. Primary outcomes are documented controlled blood pressure, serum cholesterol, and prescription of recommended preventive medication (effect evaluation).

2. To determine the potential effect of the program on other indicators for CVRM, self-reported goal attainment in the intervention group, and unintended consequences. Secondary outcomes are all other indicators for CVRM, self-reported goal attainment in the intervention group, and unintended consequences (effect evaluation).

3. To determine the economic efficiency of the program in the observed period regarding the primary outcomes.

4. To explore what factors and mechanisms are associated with change (or absence of change) of performance in CVRM.

## Methods/design

### Trial design

The study design is a cluster randomized controlled trial with a block design, considering primary care practices as units of clustering.

### Ethical approval and informed consent

The Medical Ethics committee Arnhem-Nijmegen waived approval for this trial. At follow-up practices will send a letter of invitation and informed consent to 100 patients with established CVD. Patients return their letter with informed consent to Radboud University Nijmegen Medical Centre with permission for audit of their medical records. The privacy of the participating patients will be protected, and all data will be coded and processed anonymously. For the baseline-measurement, mandatory information on indicators for patients with established CVD will be used, collected by practices on behalf of the practice accreditation program.

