#### Patients

The study focuses on patients with established CVD. This includes patients with angina pectoris, acute myocardial infarction in their medical history, other chronic ischemic heart diseases, transient ischemic attack (TIA), ischemic stroke, peripheral arterial disease, and aneurysma aortae. Selection of patients out of electronic medical records with these conditions will be based on corresponding diagnostic International Classification of Primary Care codes (ICPC-codes K74, K75, K76, K89, K90.3, K92.1 and K99.1), a worldwide system to label conditions in primary care [18].

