#### The practice accreditation program

The practice accreditation program is an existing procedure provided since 2005 by an independent body (NPA) that has a license to use the accreditation procedure developed by the DCGP. The DCGP remains responsible for the content and further development of the procedure; it will be responsible for adequate delivery of the practice accreditation program in this study. The practice accreditation program comprises, firstly, of a comprehensive audit (using validated performance indicators) and written feedback to the practice, which covers a range of clinical domains (mainly chronic diseases), practice management, and patient experiences. The feedback, which consists of a comparison with benchmarks of other primary care practices, is discussed with a non-physician observer in a feedback consultation and helps to identify substandard performance. The second obligatory component, the planning of improvements in the practice according to the principles of quality management, is based on this feedback. The practice team is supported by a trained non-physician consultant. Practices that perform the procedure as planned are all accredited, so accreditation does not imply that a certain minimum score has been obtained (the latter is usually labeled certification). In the practice accreditation program, validated instruments are used: the Visit Instrument to asses Practice management (*Visitatie Instrument Praktijkvoering*, VIP) [19], clinical performance, and Europep [20]. Practices in the program receive a reimbursement of some insurance companies consisting of a bonus per patient per year. Furthermore they receive a certification for the time period of one year that demonstrates (to the public) their involvement in continuous quality improvement. Every year the practice will be audited, and every year new improvement plans have to be formulated that have to be approved by the auditor.

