#### Measurement procedures

In each practice measurements are done at baseline and at follow-up (Figure 1). At baseline, medical records of 40 patients with established CVD are audited as part of the clinical performance measurements in the practice accreditation program. Data on performance indicators of CVRM as included in the practice accreditation program will be used for the analysis. At follow up, the following measurement methods will be used: medical record audit based on the same indicators of CVRM as in the baseline measurement, patient questionnaires, and a semi-structured interview for a contact person in each practice. Data will be collected consistently as this is done by two persons with similar training.

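### Follow-up primary outcomes come only from patients who consent to an invitation from practices that know their allocation, so selection after randomisation could bias the comparison between arms

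*Protocol article*

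**What the plan says.** All references are to the protocol article.

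- **Follow-up sample.** Under Ethical approval and informed consent: "At follow-up practices will send a letter of invitation and informed consent to 100 patients with established CVD". Then: "Patients return their letter with informed consent to Radboud University Nijmegen Medical Centre with permission for audit of their medical records". Measurement procedures makes a medical record audit the follow-up source of the indicators, three of which are the primary outcomes.
- **Baseline sample.** Ethical approval and informed consent: "For the baseline-measurement, mandatory information on indicators for patients with established CVD will be used, collected by practices on behalf of the practice accreditation program". Measurement procedures: "At baseline, medical records of 40 patients with established CVD are audited as part of the clinical performance measurements in the practice accreditation program". No individual consent step is described.
- **Order of events.** Intervention group places randomisation after baseline data collection. That section and Control group tell each arm which domain to work on, so practices know their allocation when they send the letters.
- **Who counts as a patient.** Patients: "Selection of patients out of electronic medical records with these conditions will be based on corresponding diagnostic International Classification of Primary Care codes". Measures of effectiveness defines each primary outcome as a percentage of the practice's patients with known established CVD, not of those who consent.
- **Analysis.** Statistical methods plans a logistic model in group and measurement moment, with random coefficients for practice and adjustment for baseline differences between the groups.

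**The concern.** Randomising practices makes the practices comparable. It does not protect a patient sample that is formed after allocation by people who know the allocation. Three steps decide who enters the follow-up denominator: who carries a CVD code, who receives a letter, and who replies. Intervention practices spend the study period working on CVD care, and control practices are told not to. Each step could therefore run differently in the two arms. For example, closer contact with well-controlled patients might make those patients more willing to consent.

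Baseline patients did not pass through the consent step and were sampled before allocation. A baseline term therefore carries no information about a difference in follow-up selection. All three primary outcomes share the exposure, and so do the cost-effectiveness ratios built on them. It cannot be repaired once the data are in.

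**Working it through.** **1. The plan's own figure.** Inputs from Sample size: 55% against 65%, power 0.80, alpha 0.05 (taken as two-sided), ICC 0.05, 30 patients per practice.

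- n per arm = [1.96·√(2·0.60·0.40) + 0.842·√(0.55·0.45 + 0.65·0.35)]² / 0.10² = 376 after rounding up.
- Design effect = 1 + 29·0.05 = 2.45, and 376·2.45 = 921 patients.
- 921/30 = 30.7, so 31 practices per arm.

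The stated 31 reproduces. The sample size is not in question. It supplies the scale: a 10-point target and an expected effect of 5 to 10 points.

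**2. Effect of the consent filter on an observed rate.** Let p be the true proportion controlled, c1 the consent rate of controlled patients and c0 that of uncontrolled patients:

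observed rate = p·c1 / [p·c1 + (1 − p)·c0]

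The documents give no consent rates. Those below are assumptions, with p = 0.55 in both arms and no true effect.

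| c1 | c0 | Calculation | Observed |
|---|---|---|---|
| 40% | 30% | 0.220/(0.220 + 0.135) | 62.0% |
| 45% | 30% | 0.2475/(0.2475 + 0.135) | 64.7% |
| 50% | 30% | 0.275/(0.275 + 0.135) | 67.1% |

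- First row in both arms: 62.0% against 62.0%, so no spurious difference. The rise of 7.0 points over 55% is a shift in level, not a bias between arms.
- First row in one arm, second in the other: 64.7 − 62.0 = 2.7 points.
- First row in one arm, third in the other: 67.1 − 62.0 = 5.1 points.
- Exchanging the arms reverses the sign, so the same mechanism could hide a real effect.

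**3. Whether baseline removes it.** In the 45%/30% case both arms start at 55%. The changes are 64.7 − 55 = 9.7 and 62.0 − 55 = 7.0 points, and their difference is still 2.7. On the odds scale the baseline odds ratio is 1 and the follow-up one is (45/30)/(40/30) = 1.125, or 1.25 with 50%/30%. The change from baseline reproduces the bias in full. The planned effect corresponds to (65/35)/(55/45) = 1.52.

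**4. Sensitivity.** Let R = c1/c0 in one arm, with no selection in the other and no true effect. Effective size per arm is 31·30/2.45 = 380, and the last column ignores any gain from baseline.

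| R | Spurious difference at p = 55% | Chance of a significant result at nominal 5% |
|---|---|---|
| 1.10 | 2.4 points | about 10% |
| 1.25 | 5.4 points | about 33% |
| 1.50 | 9.7 points | about 78% |

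Starting from the programme medians of 36%, 38% and 53% gives similar results. R of about 1.23 produces 5 points.

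**The case against.** The strongest reply is that a bias between arms is assumed, not shown. Selection that is equal in both arms leaves no spurious difference under the null, and nothing in the article says that consent will differ. Replies go to the university centre and not to the practice, so practices do not handle them. Intervention practices are told to set process and outcome targets, not merely to improve registration, which limits differential coding. Patient age, gender and multi-morbidity are measured at follow-up, so some case-mix adjustment is possible. A full protocol may also say how the 100 patients are drawn.

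Much of this stands. It limits the point to a risk of unknown size and direction. It does not remove that risk: returning consent to the centre does not prevent selective invitation, the instruction on targets does not exclude changes in coding, and case-mix adjustment does not remove consent that depends on the outcome itself. The practice-sent letter and the consent restriction are stated in the article and do not rest on its silence.

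Two stronger readings are tempting and not supported.

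- A reader might call the baseline audit unselected. The article does not say how the 40 records are chosen, and the practices collect the data. It supports only that they were collected before randomisation with no consent step described.
- A reader might see a contradiction with "Data will be collected consistently as this is done by two persons with similar training". That sentence follows the list of follow-up methods and can be read as describing follow-up alone.

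**Conclusion.** The point holds as a risk of bias that should be fixed, not as a demonstrated bias. The follow-up sample is formed after allocation by invitation from practices that know their arm, and is then limited to those who consent. The outcomes are defined on all known CVD patients in the practice, and the planned model cannot correct selection that differs by arm. Under the assumed consent rates the spurious difference is 2.7 to 5.1 points, against an expected effect of 5 to 10 points. These figures show that a modest difference in consent would matter; they do not predict that it will occur. That practices know their allocation is inferred from the arm-specific instructions.

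**What to change.** 1. **Freeze the list.** Extract each practice's code-based list of CVD patients at baseline, before randomisation, and hold it unchanged.
2. **Draw centrally.** At follow-up, have the research team draw the 100 invitees at random from that list. The practice only posts the letters.
3. **Adjust.** The first two steps address coding and invitation but leave the consent filter in place. Adjust the follow-up comparison for the patient age, gender and multi-morbidity already to be collected (Other measures). This is a partial correction.
4. **Sensitivity analysis.** The practice accreditation program section says "Every year the practice will be audited". Where that audit holds the same indicators at a time comparable with the trial's follow-up, analyse it as a check free of the consent filter. It should not become the primary source: at baseline the practices collect the programme data, and at follow-up they would do so knowing their allocation. The article also does not confirm that the timing matches.

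**Cost.** One list extraction per practice, a central draw and a protocol amendment. Patients newly diagnosed after baseline leave the primary denominator, so the outcome definition would have to refer to CVD known at baseline.

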#### Measures of effectiveness

The effect evaluation aims to determine the effectiveness of the program on primary performance indicators for CVRM and to determine the potential impact of the program on other indicators for CVRM, self-reported goal attainment in the intervention group, and unintended consequences.

Primary outcomes have been selected from the 20 quality indicators for established CVD [21], which were developed by DCGP (Table 1), and are:

1. The percentage of patients in the practice with known established CVD who have systolic blood pressure below 140 mmHg.

2. The percentage of patients in the practice with known established CVD who have LDL cholesterol below 2.5 mmol/l.

3. The percentage of patients in the practice with known established CVD with a record that aspirin, an alternative anti-platelet therapy, or an anticoagulant has been prescribed.

**Table 1 T1:** Indicators for cardiovascular risk management

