#### Statistical methods

The study groups will be compared at baseline regarding known determinants of cardiovascular care and its improvement. These include patient factors [27,28] (*e.g.*, age, multi-morbidity, ethnicity at practice level) and practice characteristics [22,29] (*e.g.*, availability of nurses, delegation of medical tasks to assistance, practice size). Only factors emerging from previous research are considered to avoid overcorrection in the primary analysis. A logistic regression model will be constructed for each outcome to analyze these outcomes in relation to group (intervention, control) and measurement moment (baseline, follow-up). Identified differences between the groups at baseline will be included in this analysis. Random coefficients will be included to allow for the clustering of data within practices. Each of the secondary outcomes (clinical and organizational indicators) will also be analyzed in this way. Finally, if an internally consistent scale can be constructed (reflected by high reliability coefficients of the combined score), we will develop an aggregated measure of outcome, and use this in a similar random coefficients linear regression analysis.

To identify the effectiveness of this program on attainment of practice-defined goals and its perceived unintended consequences, the second key objective, a descriptive analysis will be performed aimed at determining what proportion of self-defined goals for improvement was achieved by the practices and straightforward listing of the GP views on unintended consequences of the practice accreditation program.

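### Follow-up indicators come only from patients who consent after open allocation, while baseline needs no consent, so an outcome-related consent difference between arms would pass for a programme effect

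*Protocol article*

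**What the plan says.** The two measurements select patients differently.

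- **Baseline.** Ethical approval and informed consent: "For the baseline-measurement, mandatory information on indicators for patients with established CVD will be used, collected by practices on behalf of the practice accreditation program". Measurement procedures gives the number: "At baseline, medical records of 40 patients with established CVD are audited". No patient consent step is described.
- **Follow-up.** The same ethics section: "At follow-up practices will send a letter of invitation and informed consent to 100 patients with established CVD". Then: "Patients return their letter with informed consent to Radboud University Nijmegen Medical Centre with permission for audit of their medical records". Measurement procedures makes a medical record audit on the same indicators the source of the follow-up data.
- **Order of events.** Under Intervention group, practices are randomised once baseline data are in and are then told to work on cardiovascular disease. Under Control group, the others are told to work elsewhere. The consent letters go out afterwards, from practices that know their allocation.
- **Outcome.** Measures of effectiveness defines the first primary outcome as "The percentage of patients in the practice with known established CVD who have systolic blood pressure below 140 mmHg". The other two have the same denominator.
- **Analysis.** Statistical methods sets up a logistic regression for each outcome, "to analyze these outcomes in relation to group (intervention, control) and measurement moment (baseline, follow-up"), with adjustment for group differences found at baseline and random coefficients for practice.

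**The concern.** Randomising practices makes the two sets of practices comparable. It does not make the patients who later agree to be audited comparable, because agreement comes after allocation and is sought by unblinded practices, one arm of which has spent the period working on exactly these patients. A well-controlled patient in an intervention practice may be readier to return the form than a poorly controlled one, and this tendency need not be equally strong in control practices.

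The baseline cannot correct for this. It carries no consent selection, so the selection appears only at follow-up and is absorbed into the difference between arms in change over time. All three primary outcomes are exposed, as are the cost-effectiveness ratios that use them as denominators.

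**Working it through.** **The plan's own figure.** Sample size gives 55% v 65%, power 0.80, alpha 0.05, ICC 0.05 and 30 patients per practice.

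- Per arm without clustering: n = [1.96·√(2·0.60·0.40) + 0.842·√(0.55·0.45 + 0.65·0.35)]² / 0.10² = 376.
- Design effect: 1 + 29·0.05 = 2.45.
- Practices per arm: 376·2.45/30 = 30.7, so 31. This matches the article, and the sample-size arithmetic is not at issue.

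**Room for selection.** With 100 invited and 30 needed, the planned size is reached even if 70 of 100 patients do not consent.

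**Bias in one arm.** Let p be the true proportion controlled, and c1 and c0 the consent rates among controlled and uncontrolled patients. The proportion seen among consenters is p·c1 / (p·c1 + (1−p)·c0). Take p = 0.55 in both arms, no programme effect, and neutral consent in one arm. The consent rates below are assumptions; the article gives none.

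- c1 = 0.33, c0 = 0.30: 0.1815/0.3165 = 57.3%, a false effect of 2.3 points.
- c1 = 0.35, c0 = 0.28: 0.1925/0.3185 = 60.4%, a false effect of 5.4 points.

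**When the arm contrast is little affected.**

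- Consent of 50% in one arm and 70% in the other, unrelated to control: both arms show 55%, so the bias is zero.
- Consent of 55% v 45% (controlled v uncontrolled) in both arms: both show 59.9%. The arm difference stays at zero, but each arm appears to rise 4.9 points from baseline. A true 10.0-point effect (55% v 65%) would be seen as 69.4 − 59.9 = 9.5. With 60% v 40% in both arms it would be 73.6 − 64.7 = 8.9.

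**Effect on the error rate.** For an unadjusted follow-up comparison, the null SE is √(2·0.55·0.45·2.45/(31·30)) = 0.0361.

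- Bias of 2 points: 0.020/0.0361 = 0.55; two-sided rejection is about 9%.
- Bias of 5 points: 0.050/0.0361 = 1.38; two-sided rejection is about 28%.

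For a comparison of changes (40 baseline and 30 follow-up records, 31 practices per arm), Var = (2/31)·0.2475·[(0.05 + 0.95/40) + (0.05 + 0.95/30) − 2·0.05·r], where r is the correlation of practice effects over time. SE is 0.0498 at r = 0 and 0.0297 at r = 1, so a 5-point bias gives about 17% to 39%.

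**What adjustment for pre-randomisation status achieves.** Assume 55% controlled beforehand, and follow-up control of 75% if controlled before and 30.6% if not (overall 0.55·0.75 + 0.45·0.306 = 55.0%).

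- Consent depends on earlier status (35% v 28%): consenters are 60.4% previously controlled, so 0.604·0.75 + 0.396·0.306 = 57.4%. The crude bias is 2.4 points, and it is zero within levels of earlier status.
- Consent depends on follow-up status (35% v 28%): among the previously controlled, 0.2625/0.3325 = 78.9% (+3.9). Among the others, 0.1071/0.3014 = 35.5% (+4.9). Weighted, 0.55·3.9 + 0.45·4.9 is about 4.4 points, so 4.4 of the 5.4 points remain.

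**The case against.** Several stronger readings are tempting, and the article does not support them.

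- **A reader might infer that any arm difference in consent biases the result.** It does not. A difference in level alone gives none; consent must relate to the outcome, and differently by arm.
- **A reader might infer that unlike samples at the two moments are enough to bias the arm contrast.** Selection shared by both arms largely cancels, as shown above. It mainly spoils the time trend and representativeness.
- **A reader might infer that consenters cannot be compared with the baseline sample.** That is not established. Measures of effectiveness promises patient-level indicator data with linkage to patient characteristics, and Statistical methods names age and multi-morbidity in the baseline comparison. Other measures, however, places the collection of these confounders at follow-up, so the text is mixed.
- **A reader might take 28% as the trial's false-positive rate.** It belongs to an unadjusted follow-up comparison under an assumed bias. The planned model uses both moments.

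There are also real safeguards. Forms go back to the university centre, not the practice. Two similarly trained people collect the data, and the audit is standardised. These protect the handling of forms and the measurement. They do not affect which patients choose to reply.

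It is also fair that a report of consent by arm may sit in a fuller protocol, so its absence is not criticised here. What stands is a design feature that the article states itself: who is audited, when, and at whose invitation.

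**Conclusion.** The point holds in limited form. Follow-up measures the primary outcomes among consenters recruited after open allocation, not among all patients with known CVD in the practice. An outcome-related difference in consent between arms would be read as a programme effect, and neither the baseline measurement nor adjustment for baseline differences can remove it.

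The actual size, and even the direction, are unknown. The 2.3 to 5.4 points rest on assumed consent rates, with selection placed in one arm only. They show that modest selection could reach the lower end of the 5 to 10 points the trial expects, not that it will. This is an important weakness that is cheap to reduce, not one that invalidates the trial. Confidence is high on what the article says and moderate on how much it matters.

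**What to change.** 1. **Extract earlier values from the same record.** When a consenting patient's record is audited, also take the last systolic blood pressure, LDL cholesterol and antithrombotic status dated before that practice's randomisation, and adjust the primary analysis for them. Keep the unconsented 40-record sample as the practice-level baseline. This removes selection on earlier status. It also adds power: from 0.81 at 10 points (SE under the alternative √((0.2475 + 0.2275)·2.45/930) = 0.0354) to about 0.89 to 0.90 if earlier status explains 20% to 25% of the variance, an assumed range. It does not remove selection on status that changed after randomisation. The cost is some extra minutes per record already open, and a check that the consent wording covers earlier entries.

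2. **Add an unconsented comparison for the remainder.** The section on the practice accreditation program says practices are audited every year. Ask the programme for the same mandatory indicator report at follow-up as at baseline, and report its arm difference as a sensitivity analysis. State beforehand what disagreement counts as material and that the conclusion will then be qualified. The cost is one data request and one analysis paragraph; it must first be confirmed that the yearly audit repeats these indicators. The drawback is that these data are collected by unblinded practices, so they serve as a check and not as a replacement.

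Reporting consent by arm, set against the characteristics of those invited, is a useful description but does not correct the estimate.
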